### ‘10 steps 2 outrun injuries’ prevention programme

Participants in the intervention group will get access to the online ’10 steps 2 outrun injuries’ prevention programme. This prevention programme was developed by experts in the field, including human movement scientists, sport physicians, the medical committee of the Dutch Athletics Federation and a sport physiotherapist, based on literature, the expertise of the clinicians and researchers and the results and expertise of our previous trial.^10 11^ The developed ’10 steps 2 outrun injuries’ programme includes 10 steps that all deal with one item related to RRI prevention. Because the aim was to develop a directive and personalised prevention programme, the advices in the programme can be easily applied to running practice and most advices are adaptable to the personal situation of the runners. During the development process, the content and lay-out were discussed with a panel of five recreational runners and their input was taken into account during the development of the RRI prevention programme. In accordance with the preferences of recreational runners, the prevention programme is available on a website and mobile application.^13^ To increase the attractiveness and usability of the prevention programme, the use of text is minimalised and the advices are explained by means of infographics, videos and animations.

All participants randomised to the intervention group will receive a personal login code (username and password) by email. These codes are also used to register the frequency of use of the prevention programme (including the use of the specific elements) of the participants.

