#### Step 7: wear shoes that feel comfortable

Many runners believe that running shoes play an important role in the occurrence of RRIs.^13 36^ However, so far it has never been shown that RRIs can be prevented by wearing a certain type of shoes or by matching the shoe to the foot morphology.^37–39^ Therefore, runners are made aware of this and are advised to wear shoes that feel comfortable. This information is provided by an interview with an expert sports physician.

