#### Step 10: run with joy

### Sample size

Based on our previously conducted RCT, an injury incidence of 38% is expected in recreational runners participating in running events (10 km up to 42.195 km).^11^ The sample size calculation is based on the subgroup analysis on runners with previous injuries. With a risk difference of 5%, a significance level of 0.05 (two-sided testing and a power of 80%), a minimum of 1414 runners with a previous injury in the previous 12 months should be included in the analyses. The sample size is doubled in order to obtain enough power for the primary analyses in the entire study population. Taking a loss to follow-up of 20% into account, a total of 3394 runners (1697 in each group) should be included.

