### Statistical analysis

Because the follow-up period of this study is at least 3 months, participants who filled out the baseline questionnaire less than 60 days before the running event will be excluded from the analyses. Descriptive statistics and their corresponding SD and frequency distributions will be calculated for all variables. Consistent with the Consolidated Standards of Reporting Trials statement, intention-to-treat analysis will be performed.^47^ Injury proportions, defined as the percentage of runners who reported a new RRI during follow-up, with 95% CIs will be calculated for all participants and for the intervention and control group separately. The injury proportions of the intervention and control group are compared by calculating the difference with 95% CI. Additionally, ORs with 95% CI will be calculated using univariate logistic regression analysis. Adjusted analysis including potential confounders (eg, age, body mass index and earlier injuries) will be performed using multivariate logistic regression analysis. Subgroup analyses are performed for the following characteristics: previous injuries in the 12 months before the trial, sex, running experience, suffering an RRI at baseline, distance of running event registered for and injury locations. Furthermore, the injury proportion of participants in the intervention group who were compliant with the prevention programme will be compared with the injury proportion of the control group. Participants are regarded as compliant if they indicated in the last follow-up questionnaire that they applied at least one of the advices from the prevention programme to their training sessions. Furthermore, an explorative additional analysis on the number of used steps in relation to the injury risk will be performed. All analyses will be performed in SPPS Statistics 25 and p values <0.05 are regarded as statistically significant.

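### The planned compliance comparison sets self-selected, outcome-aware compliers against the whole control group; it should be a randomisation-based complier estimate, with the present contrast kept as descriptive only

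*Protocol article*

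**What the plan says.** The Statistical analysis section makes intention-to-treat the analysis principle. After listing the subgroup analyses, it adds a further comparison in which all controls serve as comparator: "the injury proportion of participants in the intervention group who were compliant with the prevention programme will be compared with the injury proportion". Compliance is defined by this rule: "Participants are regarded as compliant if they indicated in the last follow-up questionnaire that they applied at least one of the advices".

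Four other places bear on this:

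- **Table 2, footnotes.** The questions on reading and applying the programme are put once, to the intervention group only, in the questionnaire sent 1 month after the event.
- **Outcome measures.** The primary outcome window runs from study registration to that same point.
- **Programme description.** On the personal login codes: "These codes are also used to register the frequency of use of the prevention programme". The record goes down to single elements.
- **Step 6 and Discussion.** Step 6 adapts training in response to pain. The Discussion concedes that following it for long enough can itself meet the injury definition.

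The further analysis of the number of steps used is called explorative. The compliance comparison has no such label, and the section's 0.05 significance threshold is stated without exception.

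**The concern.** One side of the comparison is chosen by what runners did and reported after randomisation; the other side is not selected at all. Nobody in the control group is identified who would have complied if offered the programme, so randomisation no longer makes the two sides alike.

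Three features add to this:

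- Compliance is recalled when the injury outcome is known. An injured runner may remember more (the pain prompted action) or less (training stopped).
- A complier must have returned the last questionnaire. No such condition is stated for controls.
- Because Step 6 is triggered by pain, an emerging injury can itself make a runner compliant, and acting on the advice can turn the complaint into a countable injury.

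The bar is also low. One advice of ten is enough, including Step 7, where "runners are made aware of this and are advised to wear shoes that feel comfortable". The definition may therefore separate users from non-users poorly.

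At stake is how a secondary result is read. A complier contrast could suggest benefit or harm where the randomised comparison shows none, or could mask a real benefit.

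**Working it through.** **Inputs from the protocol.** Sample size section: "an injury incidence of 38% is expected in recreational runners participating in running events"; a risk difference of 5 points; two-sided 0.05; 80% power; 1697 per group; 20% loss. As a check on the benchmark, 38% versus 33% needs 1437 per group by the usual two-proportion formula. That is close to the stated 1414 if 1414 is read as a per-group number, and 1414 × 2 × 1.2 = 3393.6, the stated 3394. So 38% falling to 33% is the right yardstick. (How the section words 1414 is a separate matter.)

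**Not in the protocol.** The share who will be classed compliant, and how reporting differs by injury status. Both are assumptions below, shown over a range.

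**1. Reporting that depends on the outcome, no programme effect.** Let a1 and a0 be the probabilities of reporting at least one applied advice among injured and uninjured intervention runners. Then

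complier risk = 0.38·a1 / (0.38·a1 + 0.62·a0), against 38% in controls.

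| a1 | a0 | Share compliant | Complier risk | False difference (points) |
|---|---|---|---|---|
| 95% | 85% | 0.361 + 0.527 = 0.888 | 40.7% | +2.7 |
| 85% | 95% | 0.323 + 0.589 = 0.912 | 35.4% | −2.6 |
| 80% | 70% | 0.304 + 0.434 = 0.738 | 41.2% | +3.2 |
| 60% | 70% | 0.228 + 0.434 = 0.662 | 34.4% | −3.6 |
| 50% | 60% | 0.190 + 0.372 = 0.562 | 33.8% | −4.2 |
| 60% | 50% | 0.228 + 0.310 = 0.538 | 42.4% | +4.4 |
| 40% | 30% | 0.152 + 0.186 = 0.338 | 45.0% | +7.0 |
| 50% | 70% | 0.190 + 0.434 = 0.624 | 30.4% | −7.6 |

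The first seven rows have a 10-point reporting gap, the last a 20-point gap. With more than half classed compliant, none of these 10-point gaps reaches 5 points. It takes a lower compliance level or a wider gap.

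**2. Selection in general, no programme effect.** Let c be the share compliant and D the risk of non-compliers minus that of compliers. Randomisation gives 0.38 = c·p(complier) + (1 − c)·p(non-complier), so

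complier risk − 0.38 = −(1 − c)·D.

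- c = 0.5, D = 10 points: false benefit 0.5 × 10 = 5.0 points. With about 1358 analysed per arm (0.8 × 1697) and 679 compliers, this is nominally significant about 60% of the time.
- c = 0.7, D = 15: 0.3 × 15 = 4.5 points.
- c = 0.9, D = 10: 0.1 × 10 = 1.0 point. Reaching 5 points here would need D = 5/0.1 = 50 points.

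**3. A real effect hidden.** Suppose the true intervention risk is 33%, and 75% of injured and 60% of uninjured runners report applying an advice. Complier risk = 0.2475/(0.2475 + 0.402) = 38.1%, which is 0.1 point above control. The 5-point benefit disappears.

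**4. The alternative.** The complier-average effect is the intention-to-treat difference divided by c. With no programme effect the numerator has expectation zero, whatever c is and whoever complies. Treating c as fixed, the interval is 1/c times as wide as the intention-to-treat interval, for example twice as wide at c = 0.5.

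**The case against.** The strongest reply is that this is a supplementary analysis. It is not among the listed outcomes, intention-to-treat governs the main comparison, and the documents nowhere say that a null result will be reinterpreted through it. That stands. The Introduction does draw hedged lessons from applied-versus-not-applied comparisons in the predecessor trial, which supports clear labelling but does not predict what this trial will conclude.

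A reader might infer that the bias will be as large as the 5-point target. The documents do not support that: they give no compliance figures, and the size depends on the compliance level assumed. Two of the criticisms also pull apart. If one advice in ten makes almost everyone compliant, selection bias shrinks. That is right, but the comparison then says little that intention-to-treat does not.

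A reader might also infer that the login data go unused. They are absent from the compliance definition, but the number-of-steps analysis names no data source and may draw on them.

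The remedy has limits too. Logins record use, whereas Table 2 separates reading from applying. The Measurements section says that newsletters to the intervention group highlight programme content, so runners who never log in still receive some of it. That strains the assumption that assignment acts only through compliance, and a stricter threshold on steps would strain it further. Restricting to runners to whom Step 1 does not apply cannot be done cleanly: Step 1 concerns runners with no previous injury, while the baseline item covers only the previous 12 months. These points shape the fix; they do not rescue the planned contrast.

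**Conclusion.** The point holds for a supplementary analysis and is a cheap improvement. As written, the comparison is non-randomised and can differ from zero when the programme does nothing, in a direction that cannot be known in advance. That much follows from the text alone.

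The size rests on assumed reporting rates. For the 10-point reporting gaps examined with more than half classed compliant, it is 2.6 to 4.4 points. It passes 5 points only with lower compliance or a wider gap, such as 7.6 points for 50% versus 70%. It shrinks when about 90% or more are classed compliant.

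Nothing here touches the primary intention-to-treat result, and it should not be read as a flaw in the trial's main conclusion.

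**What to change.** In the Statistical analysis section:

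1. Make the compliance analysis a complier-average causal effect: the intention-to-treat risk difference divided by the proportion of the intervention arm that complied, with a 95% CI.
2. Define compliance inclusively, as any programme use recorded through the login codes. This is recorded independently of the last questionnaire and does not depend on recall. Use self-reported application of at least one advice as a sensitivity definition.
3. State the exclusion restriction, and say that the intervention newsletters highlighting programme content may strain it.
4. Keep the complier-versus-control comparison and the number-of-steps analysis as descriptive only, with no p-value and no claim of effectiveness.
5. Do not add a stricter step threshold or a Step 1 restriction.

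The cost is a change of wording and the use of data already collected. The downside is a wider interval and an assumption that cannot be tested.

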### Patient and public involvement

A group of give recreational runners were invited at Erasmus MC during the preparation phase of the study. At this meeting, the content and design of the prevention program were discussed and all delivered input for improvement. Moreover, these runners had a critical look at the questionnaires and delivered input for improvement.

## Discussion

Injuries are a major problem among runners, for which no effective prevention measures have been identified so far. Therefore, the aim of this RCT is to examine the effectiveness of an online injury prevention programme. This programme is aimed at runners who previously suffered from RRIs and includes 10 steps that all deal with one component of running injury prevention. The programme is tested in a large group of runners. Therefore, subgroup analyses based on previous injuries, sex, running experience, distance of running event registered for and injury locations will be possible. Because the programme is presented on a website and mobile application, the programme has the ability to be easily implemented and applied to large and diverse groups of runners if it proves to be effective.

A potential limitation of this study is the use of self-reported RRIs. Runners who are performing with pain may give diverse responses regarding the presence of an RRI. This is partly solved by including the OSTRC Overuse Injury Questionnaire in the follow-up questionnaires, which gives more insight in the severity of the reported RRIs. However, also this questionnaire is patient-reported and subject to the interpretation of the runners. Another possible limitation is that some of the advices in the prevention programme may be subject to the interpretation or motivation of the runners. A runner may, for example, adjust the score on the Numerical
Rating Scale (NRS) pain scale depending on whether the runners is keen on performing the next training, which could potentially influence the effectiveness of the prevention programme. A third potential limitation is the fact that most steps of this preventive intervention programme are designed based on existing scientific knowledge but without exact knowledge of the ‘optimum advice’ for a specific group of runners. For example, we proposed a ACWR cut-off value of 1.5 which was based on research in several team sports and which was feasible with regards to the currently proposed training schedules of the national healthcare organisations. We are—however—not sure whether this cut-off value is ideal for a large group of runners or whether it is effective to use for a subgroup of runners. Finally, a possible limitation is that one topic of the prevention programme may interfere with the definition of an RRI. In step 6 of the prevention programme, runners are advised to stop running or adapt their training when they experience the first signs of an RRI (uncomfortable or mild pain during running) in order to prevent an RRI that will cause prolonged absence from running. However, if they reduce their running for more than 7 days or three consecutive training sessions because of this advice, the pain should be considered as an injury according to our definition of an RRI. Even though we do believe that the advice of step 6 may be an effective way to reduce the injury risk, this advice may therefore interfere with our primary outcome. To explore this, the injury proportion of runners who indicate that they applied the information from step 6 is compared with the injury proportion of runners in the intervention group who did not apply this information. By doing so, we can estimate the impact of this advice on the actual reported number of injuries.

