#### Step 6: do not ignore pain during and after running

The majority of the RRIs are overuse injuries.^34^ These injuries usually start as an uncomfortable feeling or mild pain during running, that increases in severity over time. When runners experience these first signs of an RRI, it is probably wise to adapt training activity accordingly or temporarily stop running. Therefore, the prevention programme includes a 0 to 10 NRS pain scale (0 points means no pain and 10 points means maximum pain imaginable) that guides runners in continuing, skipping or altering the next training session.^35^ After a training session, runners should score the amount of pain during and directly after running. In case of a pain score above 5, the runners are recommended to skip the next training session. When the pain score is between 2 and 5, the advice is to alter the intensity and distance of the next training session. A score lower than 2 results in the advice to continue running.

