### Outcome measures

The primary outcome measure of the SPRINT study is the difference in injury proportion between the intervention and the control group in the time period between the registration for the SPRINT study and 1 month after the running event. An RRI is defined as a self-reported injury of the muscles, joints, tendons and/or bones in the lower back or lower extremities (hip, groin, thigh, knee, leg, ankle, foot and toes) that is caused by running (training or competition). The injury has to be severe enough to cause a reduction in running distance, speed, duration or frequency for at least 7 days or three consecutive scheduled training sessions or the injury requires that the runners consults a physician or other health professional.^46^

Secondary outcome measures include the between-group differences in (1) the severity score of running injuries (range 0 to 100), the proportion of substantial overuse injuries (both based on the OSTRC Overuse Injury Questionnaire) and injury proportion of medical attention injuries, (2) injury proportion in runners with previous injuries and (3) RRI locations.

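### Comparing self-reported Step 6 users with non-users inside the intervention arm cannot estimate how that advice affects reported injuries

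*Protocol article*

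**What the plan says.** - **The advice (Step 6 section).** Runners score their pain after each session. "In case of a pain score above 5, the runners are recommended to skip the next training session". At intermediate scores they are to modify the next session. "A score lower than 2 results in the advice to continue running". The same section describes mild pain as the usual beginning of an overuse injury.
- **The outcome (Outcome measures).** A complaint counts as an RRI by one of two routes. It must either "cause a reduction in running distance, speed, duration or frequency for at least 7 days or three consecutive scheduled training sessions", or lead the runner to see a health professional.
- **The overlap (Discussion).** The article notes that under Step 6 "runners are advised to stop running or adapt their training when they experience the first signs of an RRI", and concedes that a runner who does so for long enough then counts as injured.
- **The check (Discussion).** The comparator is "the injury proportion of runners in the intervention group who did not apply this information"; set against it is the same figure among those reporting that they used Step 6. The stated inference is: "By doing so, we can estimate the impact of this advice on the actual reported number of injuries".
- **How use is measured (Table 2 and its footnotes).** Runners report which steps they applied in the final follow-up questionnaire only, one month after the event.
- **Who is told to act (Step 1 section).** Runners with no earlier RRI are told to leave their running as it is, although they can see every step.
- **Adjustment (Statistical analysis).** The adjusted model gives age, body mass index and earlier injuries as examples of covariates. It is not tied to the Step 6 check.

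**The concern.** The article identifies a real problem: one part of the intervention can create events under the outcome definition, and only the intervention arm receives it. Randomisation does not remove such an artefact, because it is part of what differs between the arms.

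The analysis offered for it is not a randomised contrast. It splits one arm by a behaviour that pain triggers, and pain is the early stage of the outcome. If readers take the result as an estimate of the advice's impact, a difference produced by selection could be read as evidence that Step 6 adds reported injuries. That reading would then colour the interpretation of the primary result.

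**Working it through.** The article gives no figure for this check, so there is nothing to reproduce. The working has three parts: who ends up in each group, how large a false difference could be, and what the contrast would mean without selection.

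**1. Who is a user and who is not**

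- Step 6 asks for changed training only at higher pain scores, so runners with pain have more occasion to apply it. They are also the runners closer to an RRI.
- Step 1 steers runners without earlier injuries away from changing anything, and its section ranks injury history as the leading risk factor. Non-users are therefore likely to include more low-risk runners.
- Use is reported after the follow-up in which injuries are counted. An injured runner may recall cutting back as having applied Step 6.

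**2a. Size of a false difference, by uptake in injured and uninjured runners**

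Input from the article: injury proportion 0.38 (Sample size). Assumed: uptake a1 in injured and a0 in uninjured runners, with no effect of the advice on anything.

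- Injured among users = 0.38·a1 / (0.38·a1 + 0.62·a0)
- Injured among non-users = 0.38·(1−a1) / [0.38·(1−a1) + 0.62·(1−a0)]

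| a1 | a0 | Users | Non-users | Difference |
|---|---|---|---|---|
| 0.20 | 0.20 | 38.0% | 38.0% | 0 |
| 0.30 | 0.20 | 0.114/0.238 = 47.9% | 0.266/0.762 = 34.9% | 13.0 points |
| 0.40 | 0.20 | 0.152/0.276 = 55.1% | 0.228/0.724 = 31.5% | 23.6 points |

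This takes the imbalance in uptake as given. It shows what a given imbalance would produce, not that the imbalance exists.

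**2b. Size of a false difference when pain drives uptake**

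Assumed central case: half of runners have pain, pain triples the RRI risk, and uptake is 50% with pain and 20% without. The overall risk is held at 38%.

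- Risk without pain = 0.38 / (0.5·3 + 0.5) = 0.19; with pain = 0.57
- Users: (0.25·0.57 + 0.10·0.19) / 0.35 = 0.1615/0.35 = 46.1%
- Non-users: (0.25·0.57 + 0.40·0.19) / 0.65 = 0.2185/0.65 = 33.6%
- False difference: 12.5 points

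The assumptions were then varied: pain in 50–60% of runners, a risk ratio of 2–4, and uptake of 40–60% with pain against 10–20% without. The false difference runs from about 5 to 25 points. Equal uptake (30% and 30%) gives zero. For scale, the Sample size section plans for a difference of 5 points.

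**3. What the contrast would mean without selection**

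Observed difference = selection + cutbacks counted as injuries − injuries truly prevented.

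With selection at zero, one number still carries two opposing effects, so the interference cannot be separated out. With selection present, even the sign can be wrong. Suppose, in the central case, that Step 6 lowers risk by 10 points in users with pain. Averaged over all users that is 0.25·0.10/0.35 = 7.1 points. Users then show 0.1365/0.35 = 39.0%, against 33.6% in non-users, so a real benefit appears as an excess of 5.4 points (12.5 − 7.1).

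**The case against.** The strongest reply is that little depends on this check. It appears among the limitations, is presented as exploration, and enters neither the sample size nor the primary analysis, which compares the arms as randomised. That stands, and it limits the severity.

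Three further objections also have force:

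- **Other relevant outcomes are planned.** A reader might infer that this check is the trial's only protection against the artefact. The documents do not support that. Outcome measures already lists between-group comparisons of medical-attention injuries, OSTRC severity and substantial overuse injuries, and the Discussion presents the OSTRC questionnaire as giving insight into severity. What is missing is any link from these outcomes to the Step 6 problem.
- **The direction is not certain.** A reader might infer that users are bound to show more injuries. A pain-free runner who scores below 2 and carries on has also followed Step 6 and may report applying it. True prevention would pull the difference down. Upward bias is likely, not guaranteed.
- **The size is assumed.** Apart from the 38%, no input to the illustrations comes from the article. Much larger differences can be produced by assuming more extreme uptake, but nothing in the documents supports choosing such values.

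None of this rescues the inference. A full analysis plan might add detail, but the objection is to a comparison and a conclusion that the article states. The login records mentioned for programme use could reduce recall error, but not confounding by pain.

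**Conclusion.** The sentence claiming that the impact can be estimated is wrong as written. The comparison is confounded by pain and injury history, its exposure is self-reported after the outcome is known, and it cannot separate prevention from cutbacks counted as injuries.

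The bias is probably upward. Under modest assumed uptake (30% in injured, 20% in uninjured runners) it is 13 points with no effect of the advice. Under the pain-driven assumptions it is about 5 to 25 points, and it vanishes if uptake is unrelated to pain or injury. These are illustrations, not estimates for this trial.

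This should be fixed but is not critical. A reader might go further and infer that the primary result is invalid, or that Step 6 does inflate the injury count. The documents support neither: the primary comparison is unaffected by this check, and the article says only that the advice may interfere with the outcome.

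**What to change.** 1. Delete the claim that the user/non-user comparison estimates the impact of the advice. If the comparison is kept, label it descriptive and state that pain, injury history and recall drive it.
2. Prespecify that the Step 6 interference is examined between the arms as randomised, in all randomised runners, using planned outcomes that do not depend only on training reduction. Medical-attention injuries should come first, with OSTRC severity in support, reported beside the primary RRI result. The article does not list the OSTRC items, so check how far that score itself reflects reduced training.
3. If the data allow, also show by arm the RRIs that qualify only through training reduction. Table 2 lists treatment and OSTRC severity but no explicit item for which criterion was met. The full questionnaire is not shown, so this step is conditional.
4. Treat the pattern as supportive, not conclusive. A difference confined to training-reduction RRIs does not prove an artefact. The programme may truly affect milder injuries, care-seeking may differ because participants are unblinded, or medical-attention events may be too few.

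Possible wording: *Injury proportions by reported use of Step 6 will be described only. Possible interference of this advice with the RRI definition will be assessed by comparing medical-attention injuries, supported by OSTRC severity, between randomised groups.*

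The cost is a change of wording and one prespecified presentation of outcomes already collected. The downside is fewer events in each component and so wider intervals.
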